#### Aim.

In the light of the evidence, the aim of this research is to determine whether differences in user experience between the two systems; a game-based auditory discrimination training program and a non-game-based auditory discrimination training program, lead to differences in auditory discrimination perceptual, behavioral and electrophysiological performance within a normal-hearing population To meet this aim, the research will be conducted as follows:

To develop and validate a digital game-based auditory discrimination training tool.To develop a weekly program and to monitor key performance indicators (KPIs) in terms of time, accuracy and discrimination thresholds.To measure auditory processing improvement through perceptual, behavioral and electrophysiological tests comparing discrimination tasks’ performance before and after the use of auditory discrimination training system.

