**Fig 4 pone.0313478.g004:**
[figure not shown]
Auditory discrimination paradigm procedure. Basal state is only recorded at the beginning of the session. In each of the feature variation the rest of the procedure is repeated.

Sound system used for stimuli is integrated by a sound interface (DAC/ADC) with supra-aural Shure SRH 440’ headphones system calibrated to audiometric reference of 1kHz to 70 dB HL. Sound stimuli consists in pure tones lasted with 100 ms duration and with a 900 ms ISI as the standard stimuli. Deviant stimuli vary in each of the four testing sound features (pitch, intensity, duration and localization). EEG event related activity will be processed in Matlab with EEGLab, for preprocessing and epoching (−200ms, 600ms)”.

For the AT, digital tools will be shown to participants, they will be instructed in how to use it, and main features will be explained. They will be told to use it daily for 30 minutes indicating the modules to evaluate in each week sessions. Game data (training time, response time and correct responses) will be gathered for participants after each week to register in-game indicators. They will be asked not to do more or less time than indicated, if indication is not followed, they will not be eligible to continue participating. An extra explanatory video will be provided with a user manual.

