#### Group B (Experimental).

AT for game-based group will have game elements and competing resources, such as game objective, game characters and visuals, CPU competition players, feedback, time and lives management.

AT methodologies to be used are non-game based auditory training and game-based auditory training. Each tool is applied as indicated in the SPIRIT checklist in Fig 1.

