### Expected outcomes & analysis

The primary outcome measures are related to neuro audiological changes in auditory processing. AEPs to be obtained are Mismatch Negativity and P3 components (continuous). Additionally, number of discrimination trials (discrete) will be registered. The secondary outcome measures are the in-game indicators such as time in each activity (continuous), accuracy (discrete) and attempts (discrete) to relate directly changes in audiological measures and game performance. The expected outcome of ADPQ is to increase the average score, that indicates a better perceived state and performance in auditory discrimination tasks that would be correlated with the in-game indicators and the electrophysiological measurements. The expected comparison outcome for AEP, it is expected an increase in evoked potentials amplitude and a decrease in latencies. For the in-game indicators it is expected to increase accuracy answers and decrease tasks’ solving time.

Once obtained and processed KPIs and discrimination threshold results, data will be analyzed with the following tools. Each of them will compare before and after auditory training KPIs and AEPs tests.

A 2-way analysis of variance (ANOVA) with repeated measures will be done considering the following factors.

For pre & post training measurements to determine individual performance of each methodology and contrast the improvement of each (within factors).For training group. Both methodologies have a similar distribution of activities to accomplish withing the training. Each group will be evaluated to determine if some activity yielded to a more significant difference in the overall performance (between factors).Finally, and mainly, for AT methodology groups to analyze and compare the final performance between the game-based experimental groups and the non-game-based control group and conclude if there is a significant difference between them.

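### In-game KPIs enter the before/after and between-arm analysis, but they are logged only during training and by a different interface in each arm, so a between-arm difference in final KPIs is confounded with the interface

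*Protocol article*

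**What the plan says.** All references are to the protocol article.

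- **Analysis.** Expected outcomes & analysis applies its tests to KPIs as well as evoked potentials: "Each of them will compare before and after auditory training KPIs and AEPs tests". The method is a two-way repeated-measures ANOVA with pre/post as the within factor and training group as the between factor. The last item in the list is called the main one: "Finally, and mainly, for AT methodology groups to analyze and compare the final performance" between the game-based and the non-game-based arm.
- **Status of the KPIs.** The same section makes in-game time, accuracy and attempts secondary outcomes, to be related to the audiological measures. The Aim section sets out to "monitor key performance indicators (KPIs) in terms of time, accuracy and discrimination thresholds".
- **Collection.** Study design & setting says: "Game data (training time, response time and correct responses) will be gathered for participants after each week to register in-game indicators". Participants train daily, with the instructions "indicating the modules to evaluate in each week sessions". The training data are saved on each participant's own computer.
- **Interfaces.** The Group A section gives the control arm a simple graphic interface with basic right/wrong feedback. The Group B section gives the experimental arm game elements that include "CPU competition players, feedback, time and lives management".
- **Common content.** AT experimental design gives both arms the same four modules, tone-discrimination tasks and reference tones, and 15 hours of training.

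**The concern.** A before/after ANOVA needs a value before training and a value after it, and a between-arm comparison needs the same instrument in both arms. For in-game time, accuracy and attempts the text provides neither. It describes no run of the training tasks before or after training, and the two arms are scored by two different programs.

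Rules on time and lives can change how long an activity takes and how often it is attempted, whatever the player can hear. A significant between-arm result on these outcomes could then be reported as better auditory discrimination when it reflects the game's rules. The planned correlations of in-game indicators with evoked potentials and with the questionnaire (ADPQ) are open to the same problem if the arms are pooled.

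**Working it through.** **1. The plan's own figure.** Inputs from the sample size section: f = 0.25, alpha = 0.05, power 0.80, two groups, two measurements, between-within interaction. With λ = f²·N·m/(1−ρ) and N = 34, m = 2, ρ = 0.5 (assumed; the article gives no ρ):

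λ = 0.0625 × 34 × 2 / 0.5 = 8.5, on 1 and 32 degrees of freedom, power 0.807.

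The stated total of 34 is reproduced at ρ = 0.5. It would be 46 at ρ = 0.3 and 22 at ρ = 0.7. At the 40 to be recruited, λ = 10 and power is 0.869 (ρ = 0.5). The trial is thus sized on the interaction, whereas the analysis text calls the between-arm contrast of final performance the main one. That difference matters in steps 3 and 4.

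**2. What is measured where.**

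- Before and after training, by one procedure in both arms: the EEG oddball session (attentional and non-attentional), with the ADPQ given in the attentive part.
- Before allocation: audiometry.
- During training only, as far as the text describes: time, accuracy (correct responses) and attempts, from each arm's own program.

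For the third group the pre and post cells of the ANOVA are undefined.

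**3. Contrast of final values.** Assumptions: 20 per arm, two-sided 5%, identical discrimination ability, and an interface offset of d SD in the final KPI. The two-sample t statistic has 38 degrees of freedom and noncentrality d·√(20/2) = 3.162·d.

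- d = 0: 5% of trials significant
- d = 0.5: noncentrality 1.58, significant in about 34%
- d = 0.8: noncentrality 2.53, significant in about 69%

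A simulation of 20,000 trials agrees (34% and 69%).

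**4. Group-by-time interaction.** Same simulation, ρ = 0.5, supposing that an early and a late KPI value were both defined:

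- offset 0.5 SD at both times, or 0.8 SD at both times: about 5%
- offset growing from 0.5 to 0.8 SD: about 16%
- offset going from 0 to 0.5 SD: about 34%

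A constant offset cancels in the interaction. It does not cancel in the final-value contrast.

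**5. Correlations.** If the interface shifts a KPI by dx SD between arms, the arms differ by dy SD in evoked-potential change, and the within-arm correlation is zero, then the correlation pooled over arms is

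r = (dx·dy/4) / √[(1 + dx²/4)(1 + dy²/4)].

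With dx = 2 and dy = 1: r = 0.5 / √(2 × 1.25) = 0.32. Both inputs are assumptions, and with dy = 0 the pooled correlation is zero. The example shows only that pooling across arms can produce a correlation that no arm contains.

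**The case against.** The case on the other side is substantial.

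- **Both arms do the same auditory tasks.** Accuracy on the same tone comparisons carries information about hearing. A reader might infer that the KPI comparison measures the tool and not hearing. The document does not support that. It supports confounding, which is clearest for time and attempts and less certain for accuracy.
- **A common discrimination measure may exist.** The Aim lists discrimination thresholds among the KPIs and plans to compare discrimination performance before and after. The analysis section also names threshold results and a number of discrimination trials. Figs 1 and 4 are not available here. A reader might infer that no KPI of any kind exists before or after training, but that cannot be concluded. A threshold test in the assessment session would still not supply pre and post values of in-game time, accuracy and attempts.
- **Module order and difficulty are not given.** A reader might infer that early and late weeks cover different features or harder items, so that a first-versus-last-week comparison must fail. The text says only that modules are indicated week by week and that there are levels. Gradual difficulty appears as a principle from the literature, not as a stated feature of this software. If the same module and level recur, first and last exposure can be compared within an arm.
- **The interaction is protected against a constant offset.** This is correct (step 4), but the interaction needs the baseline that is not described, and the stated main contrast is final performance. That sentence does not name KPIs. They come under it because the section applies its tests to KPIs and evoked potentials alike.
- **Only secondary outcomes are affected.** This stands in full.

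**Conclusion.** The concern holds for the in-game secondary outcomes. The plan puts them into a before/after and between-arm ANOVA without describing a pre- or post-training value, and each arm's values come from its own interface. Followed as written, it can produce a between-arm result on final KPIs that reflects the interface and not discrimination ability.

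The error rates of about 34% and 69% are illustrations. They rest on assumed offsets of 0.5 and 0.8 SD, 20 per arm and no difference in ability. The article gives no figure from which the real offset could be estimated, and it may differ between time, attempts and accuracy. They apply to the final-value contrast and not to an interaction with a constant offset.

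The primary comparison of mismatch negativity and P3 uses one procedure in both arms and is unaffected. The point should be corrected before analysis, but it does not threaten the trial's main result.

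**What to change.** In Expected outcomes & analysis, replace the sentence that sends KPIs and evoked potentials through the same comparison with text to this effect:

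- Confirmatory pre/post and between-arm tests use only measures taken identically in both arms in the common assessment session: evoked potentials, responses in the attentive oddball, the ADPQ, and discrimination thresholds if they are measured there.
- In-game time, accuracy and attempts are analysed within arm, comparing first and last exposure to the same module and level. Any between-arm contrast of these indicators is labelled descriptive.
- Correlations of in-game indicators with evoked potentials and with the ADPQ are adjusted for arm.

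The cost is a change of wording and the loss of a formal between-arm test on raw in-game KPIs. The within-arm comparison needs logs that record module and level. The article does not say whether they do, so this should be confirmed before data collection.

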**Fig 3 pone.0313478.g003:**
[figure not shown]
Protocol steps. 1) Game-Based AT is first developed and validated through perceived usability evaluation questionnaires. 2) Assessments are done before and after AT is implemented for two sample groups. 3) Finally AT effectiveness is measured and compared through groups performance and AEPs.

The participant will be introduced to the study, explaining to them the informed consent and the confidentiality criteria. Participants will be given their audiometry results and a beginner game kit, also they will receive an online-shop gift card ($5-$25 us) if they finish the training levels satisfactorily, based on constant and consistent game playing, meaning they accomplish daily training and completely succeed in all training levels. Participants will also receive hearing health information after intervention and the option of scheduling a medical appointment with the otorhinolaryngologist and/or audiologist if they desire.

Auditory assessments will be conducted in noise-controlled rooms within university buildings or hospitals. Eligibility screen, informed consent and pure tone audiometry will be carried before allocation. Procedure to follow will be explained to them, beginning the pure-tone audiometry (air and bone) procedure. The participant will be indicated to raise the hand when they start to listen to the stimuli.

Then, they will be introduced to the electrode placements. Electrodes (Fz, F3, F4, Cz, C3, C4, T7 & T8) will be placed, and conductive gel will be applied to reduce the electrode-skin impedance. Calibrated headphones will be placed carefully. The participant will be asked to remain seated and still during evaluation. This process will be applied for the pre and post training assessment.

As shown in Fig 4. basal state will be recorded for 60 s in opened and closed eyes conditions. Then oddball paradigm will be used to assess auditory discrimination in pitch, intensity, duration and localization of the stimuli. P300 & Mismatch Negativity Potentials will be assessed by this paradigm in attentional and non-attentional conditions.

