### AT experimental design

AT for both groups will contain the same four modules related to auditory discrimination tasks. Each module consists of one basic acoustic feature (pitch, intensity, duration, and localization). Participants will solve pure tone discrimination tasks identifying feature differences between acoustic stimuli A from B (reference tone), and answer whether stimuli feature was higher or lower. Reference tones are centered around 0.5, 1, 2 and 4 Khz with duration of 100 ms (fade in and fade out of 5 ms). Both groups will have auditory training for an equivalent of 15 hours, with daily monitoring data and gathered every week. Training will be applied with measured and calibrated headphones given to the participants.

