The following cases are proposed to test main 2-way ANOVA with repeated measures assumptions (normality, sphericity and equal variance) [37,38]. Normal distribution will be addressed using a histogram and Shapiro-Wilk test. If no normal distribution is found, data transformation (log or sqrt) will be conducted to repeat the normality test. Treating Type I errors of heteroscedasticity, sphericity would be addressed through a Maulchy’s test. If no sphericity was found, Greenhouse-Geisser correction would be conducted to adjust degrees of freedom and repeat sphericity test. Since this study within-subjects factor (repeated measures) is only having two measurements, sphericity assumption is not required due to no covariance comparisons. If normal distribution is not corrected, repeated measures ANOVA non-parametric equivalent test will be used (Friedman’s test). An additional Barlett’s test would be done for equal variance assumption if ANOVA normality is confirmed. If equal variance is violated, robust ANOVA may be considered.

Bonferroni post-hoc test will be conducted, using multiple t-tests times p-values (to avoid increase in alpha error). Analysis software to be used is Minitab with a level of significance of 0.05.

Possible spillover effects that could bias primary outcome measures are related to 3 main conditions:

Participants discrimination performance: This effect is considered through a discrimination performance questionnaire that the participant answer to address biases during tests of outcome measures.Participants health condition (auditory pathways related): This effect is addressed through rescheduling the tests when hearing health condition is better.Participants simultaneous training: This effect is addressed in the inclusion criteria where no additional formal auditory training is performed by the participant at the time of intervention.

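### The comparison across the four sound features has no valid test as written: feature varies within participants, but the question sits in a between-factor item and sphericity is waived for a two-level factor only

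*Protocol article*

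**What the plan says.** The Expected outcomes & analysis section sets the model: "A 2-way analysis of variance (ANOVA) with repeated measures will be done considering the following factors". Three items follow.

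- The first is the time factor: "For pre & post training measurements to determine individual performance of each methodology and contrast the improvement of each (within factors", with a within-factor label.
- The second opens with training group and then turns to the activities: "Each group will be evaluated to determine if some activity yielded to a more significant difference in the overall performance (between factors".
- The third, described as the main one, compares the game-based and non-game-based groups.

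The same section names a correction, "If no sphericity was found, Greenhouse-Geisser correction would be conducted to adjust degrees of freedom and repeat sphericity test", and then sets the issue aside: "Since this study within-subjects factor (repeated measures) is only having two measurements, sphericity assumption is not required due to no covariance comparisons".

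On who does what, AT experimental design states: "AT for both groups will contain the same four modules related to auditory discrimination tasks", and "Each module consists of one basic acoustic feature (pitch, intensity, duration, and localization". For the evoked potentials, Study design & setting states: "Then oddball paradigm will be used to assess auditory discrimination in pitch, intensity, duration and localization of the stimuli". That assessment is done before and after training.

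**The concern.** Each participant contributes a value for every feature, both in training and in the oddball recordings. A comparison of one feature with another is therefore a comparison within people, over four correlated levels. The plan asks whether some activity produced a larger difference, but the only within factor it recognises is pre/post. The activity question is placed in an item labelled as between.

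What is at stake is the answer to that question. An analyst who follows the label would use an error term that includes differences between people, and could miss a real difference between features. An analyst who sees that feature is within-participant, but follows the waiver, would test four correlated levels without the correction that unequal variances or correlations call for.

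**Working it through.** **The plan's own figure.** Inputs from Sample size, inclusion & exclusion criteria: f = 0.25, alpha 0.05, power 0.80, two groups (k = 2), two measurements (m = 2). For the within-between interaction, lambda = f² × N × m / (1 − rho), with df1 = (k − 1)(m − 1) = 1 and df2 = (N − k)(m − 1). The protocol gives no rho. With rho = 0.5 assumed and N = 34, lambda = 0.0625 × 34 × 2 / 0.5 = 8.5 on (1, 32) df, and power is 0.807. At N = 32 power is 0.781, so 34 is reproduced (rho of 0 / 0.3 / 0.7 would give 66 / 46 / 22). Allowing for 10% loss, 34 / 0.9 = 37.8, or 38, which the planned 40 covers. This calculation has no feature factor, so the present point does not change it.

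**Set-up for the feature comparison.** Simulation under the null with 20,000 runs, 20 participants per group, and one pre-to-post change score per feature, giving four per participant. The correlation between a person's four scores is an assumption; 0.2, 0.5 and 0.8 are shown.

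**Case 1: feature treated as between, all rows independent.** With equal variances and a common correlation rho, a contrast between feature means has true variance proportional to 1 − rho, while the between analysis uses 1. Its standard error is too large by 1/√(1 − rho):

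- rho 0.2: 1/√0.8 = 1.12
- rho 0.5: 1/√0.5 = 1.41
- rho 0.8: 1/√0.2 = 2.24

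| rho | type I error, feature as between | type I error, feature as within | power as between* | power as within* |
|---|---|---|---|---|
| 0.2 | 0.022 | 0.050 | 0.37 | 0.51 |
| 0.5 | 0.002 | 0.050 | 0.28 | 0.73 |
| 0.8 | 0.000 | 0.047 | 0.15 | 0.99 |

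*One feature differing from the other three by 0.4 SD (assumed).

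The feature-by-group term behaves the same way: type I error is 0.021 / 0.002 / 0.000 as between. At rho = 0 there is no distortion (0.051 either way).

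**Case 2: feature treated as within, sphericity waived.** Unequal feature variances are assumed, to break sphericity:

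| SD of the four features | rho | epsilon | type I error, uncorrected | with Greenhouse-Geisser |
|---|---|---|---|---|
| 1, 1, 1, 2 | 0.3 | 0.70 | 0.064 | 0.045 |
| 1, 1, 1, 2 | 0.5 | 0.67 | 0.071 | 0.049 |
| 1, 1, 2, 3 | 0.3 | 0.66 | 0.075 | 0.050 |
| 1, 1, 2, 3 | 0.5 | 0.64 | 0.073 | 0.049 |

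Cases 1 and 2 are alternatives. A single test cannot suffer from both.

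**The case against.** The strongest reply is that the between label belongs to training group. The item opens with training group, the item before it gives time as the within factor, and a two-group, two-measurement design fits both the 2-way wording and the sample-size calculation. On that reading activity is not classified as between at all; it is a question asked inside each group. Separate 2 x 2 analyses per feature would also fit the text, and in those the waiver is correct. The article is condensed, and the detail of a subsidiary comparison could lie in an analysis plan that is not shown.

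The ambiguity is real and stands. It does not give the activity question a valid test. The comparison of the two methods has its own third item, so the activity question is what the second item adds. If the label means group only, the stated model has no activity term. Separate analyses per feature do not compare one feature with another. A comparison of activities inside each group runs over four repeated levels, which the waiver does not cover. Nor is this only missing detail, since the label, the model and the ground for the waiver are all stated.

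Two stronger readings are tempting, and the documents support neither:

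- A reader might infer that the group comparison is anti-conservative. If the four feature rows per person were stacked as independent, the standard error of the group effect would be too small by √(1 + 3 rho) = 1.26 / 1.58 / 1.84 at rho 0.2 / 0.5 / 0.8, and type I error would be about 12% / 22% / 29%. The protocol nowhere says that rows will be stacked.
- A reader might infer that the activity analysis errs in both directions at once. Treating feature as between errs one way only when correlations are positive, towards conservatism. The sphericity error arises only under the alternative, within-participant analysis.

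**Conclusion.** The point holds for the comparison across features. Feature is a four-level within-participant factor by the protocol's own description, and the stated model, factor label and sphericity waiver leave that comparison without a valid test on any reading.

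The consequence depends on which route the analyst takes: lost power if feature is handled as between, or a modest excess of false positives if it is handled as within without correction. Both sizes rest on assumed correlations and variances. The distortion in the first route vanishes at zero correlation, and that in the second vanishes if sphericity holds.

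The main group-by-time comparison, with one value per participant per time, is not touched. The waiver is right for that comparison. The point therefore concerns a subsidiary question, but one that the plan poses explicitly.

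**What to change.** In Expected outcomes & analysis:

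1. Name sound feature as a four-level within-participant factor, and keep the between label for training group only.
2. Answer the activity question with a group x time x feature repeated-measures ANOVA, applying Greenhouse-Geisser correction to every term that involves feature. Alternatively, use a mixed model with a participant random effect. A random intercept alone assumes equal variances and correlations across features, so the covariance should be allowed to differ by feature.
3. Limit the statement that sphericity is not required to the pre/post factor.

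The cost is a few sentences and slightly more analysis work. No new data or participants are needed, and the sample size stays as it is. Making the change before analysis also removes a choice that would otherwise be made with the data in hand.

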## Methods

### Sample size, inclusion & exclusion criteria

Sample Size is determined by two means; literature has worked with sample sizes averages between 10–40 participants, due to the long training period and evaluation requirements [30,31]. Sample size was calculated determining F-tests family for ANOVA repeated measures between and within interactions, given a moderate effect size of 0.25, alpha error prob of 0.05 and power of 0.80, two groups and two measurements. Effect size was determined with related previous works, where effect sizes of behavioral auditory discrimination measurements are reported from moderate to large, based on Cohen’s d and Cohen’s f calculations [32–35]. Larger effects sizes have been suggested when individuals were submitted for first time to auditory devices [36].

G*Power 3.1 points a total sample size for both groups of 34. Considering two independent groups for auditory discrimination training (ADT) implementation, sample size for Group A (control), and Group B (experimental) will be equally distributed.

A total of 40 participants will be recruited and enrolled in the study, as described in Fig 1, predicting a sample rejection of ~10%. Each of them will be randomly assigned to one of two groups (control group or experimental group) depending on the training methodology they will receive. Sample size for each group (non-game-based ADT and game-based ADT) is 20 individuals each. Assignments of each participant will be randomized using simple randomization 1:1 allocation ratio to select the group for the training methodology, avoiding bias on trials.

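### The main comparison is worded as final performance between arms, but the trial was sized for the group-by-time interaction; read as the ANOVA group main effect, it has about 37% power, not 80%

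*Protocol article*

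**What the plan says.** All references are to the Protocol article.

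- **Sample size, inclusion & exclusion criteria.** The target of the sizing is stated as follows: "Sample size was calculated determining F-tests family for ANOVA repeated measures between and within interactions". Its inputs are a Cohen's f of 0.25, a 5% significance level and 80% power, for "two groups and two measurements". The result is "G*Power 3.1 points a total sample size for both groups of 34"; 40 are to be recruited, 20 per arm. No pre-post correlation is given.
- **Expected outcomes & analysis.** A two-way repeated-measures ANOVA is planned, and three uses are listed. The first concerns pre and post measurements, "to determine individual performance of each methodology and contrast the improvement of each (within factors". The second concerns the training group and its activities and carries the between-factors label. The third is flagged as the main one: "Finally, and mainly, for AT methodology groups to analyze and compare the final performance between the game-based experimental groups". Its comparator is the control arm.

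The sentence leading into these items says that each analysis compares before with after. None of the three items names the group-by-time interaction.

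**The concern.** The aim is to learn whether game-based training improves discrimination more than non-game training. The sized test, the interaction, addresses that as a difference in change. The comparison marked as the main one is worded as a difference in final level. In a two-way repeated-measures ANOVA, that wording can be taken as:

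1. the interaction;
2. a comparison of post-training values only;
3. the group main effect, which averages each participant's post value with a pre value that cannot carry any training effect.

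These can give different p-values on the same data, and the third has far less power than stated. The article also says that those who analyse the data are not blinded, so the choice should not stay open.

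The first listed item adds a smaller risk: it could be followed by judging each arm on its own pre-post result. Two within-arm tests are not a test between arms. Both arms are trained, so a gain within one arm cannot be separated from a retest effect.

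**Working it through.** **Inputs from the article.** Cohen's f = 0.25, alpha 0.05, power 0.80, "two groups and two measurements", total N = 34 (17 per arm), 40 recruited.

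**Assumptions.** Pre-post correlation ρ is not stated; it is varied below. Expected baselines are equal because of randomisation, and the SD is the same at both times.

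**Step 1: reproduce the stated N.** For the interaction with m = 2 measurements, the noncentrality is λ = N·m·f²/(1−ρ), with 1 and N−2 degrees of freedom. At ρ = 0.5 and N = 34, λ = 34 × 2 × 0.0625 / 0.5 = 8.5, and power is 0.807. The smallest even N reaching 80% is 34, as stated. Other correlations do not give 34: ρ = 0 needs 66, 0.3 needs 46 and 0.7 needs 22. So 0.5 is a reasonable inference about what was entered, but the article does not say so.

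**Step 2: the effect behind f = 0.25.** With two groups and two times, the interaction displaces each cell mean by ±0.25 SD. The difference in change is therefore 4 × 0.25 = 1.0 SD. With equal expected baselines, this is a 1.0 SD difference at post.

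**Step 3: power of each candidate test for that same effect** (N = 34, ρ = 0.5).

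- Interaction: λ = 8.5, power 80.7%.
- Post-only: λ = N·d²/4 = 34 × 1.0²/4 = 8.5, power 80.7%. Noncentrality and degrees of freedom equal those of the interaction.
- Group main effect: averaging over pre and post halves the difference to 0.5 SD, and the variance of the average is (1+ρ)/2 = 0.75. So λ = (34/4) × 0.25/0.75 = 2.83, power 37%.
- ANCOVA on baseline: residual variance 1−ρ² = 0.75, so λ = 8.5/0.75 = 11.3, power about 90%. This is very slightly optimistic, since it ignores chance baseline imbalance.

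**Step 4: vary the correlation and N.**

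| N, ρ | Interaction | Post-only | Group main effect | ANCOVA |
|---|---|---|---|---|
| 34, 0.3 | 67% | 81% | 42% | 84% |
| 34, 0.5 | 81% | 81% | 37% | 90% |
| 34, 0.7 | 95% | 81% | 34% | 98% |
| 40, 0.5 | 87% | 87% | 43% | 94% |

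A simulation of 10,000 trials at N = 34 and ρ = 0.5 gave 0.80 (interaction), 0.81 (post-only) and 0.38 (group main effect). Reaching 80% power for the group main effect at ρ = 0.5 would need a total of 98.

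**Step 5: ANCOVA against the interaction in general.** The ratio of their noncentralities is 2(1−ρ)/(1−ρ²) = 2/(1+ρ), which exceeds 1 for every correlation below 1. At ρ = 0.5 it is 1.33. The cost is one degree of freedom.

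**The case against.** The strongest reply is that the authors mean the interaction. They size for it, plan the ANOVA that produces it, say that every analysis compares before with after, and speak of contrasting improvement. On that view this is loose English, and the exact contrast can be left to an analysis plan. The reply has force: the interaction reading is open. But the item flagged as the main one is still worded as a difference in level, so it needs correcting even if the intention was right.

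A second reply is that final performance, taken literally, means post-training values, and that averaging in the pre-training value is the less natural reading. The between-factors label does sit on the second item, not the third. This also stands. A reader might infer that the stated 80% power cannot apply to the main comparison; the figures do not support that, because the literal post-only reading keeps 80.7% under the sizing assumptions.

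Nor is it safe to say that the main-effect reading always has less than half the stated power: it has 42% at correlation 0.3, and 43% with 40 participants at correlation 0.5.

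Third, retest effects common to both arms cancel in a between-arm comparison. That is correct, and it confines the retest concern to within-arm conclusions.

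Finally, the interaction and the post-only comparison are both valid randomised comparisons, so choosing ANCOVA is an improvement rather than the repair of an invalid test.

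**Conclusion.** The mismatch is real: the trial is sized for the interaction, while the comparison called the main one is described as final performance between arms, and the interaction is not named in the analysis section.

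Its effect on power depends on the reading. With 17 per arm, a 1.0 SD difference in change, equal expected baselines and an assumed correlation of 0.5, the stated 80% holds for the interaction and for a post-only comparison. It fails for the group main effect, at 37% (34% to 42% for correlations 0.7 to 0.3). The documents do not establish that the group main effect is what will be tested. A much lower post-only figure (29%) arises only if f = 0.25 is transferred directly to the post values as a 0.5 SD difference, which is not the effect the sizing implies.

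Separately, a post-only comparison discards a baseline that is already recorded, which costs about 10 percentage points of power against ANCOVA at correlation 0.5. This should be fixed; it is a clarification with a free gain, not a flaw that invalidates the design.

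**What to change.** In *Expected outcomes & analysis*, replace the third listed item with:

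> The main test is the difference between arms in the post-training value by ANCOVA, with the pre-training value of the same measure as covariate. The group-by-time interaction, for which the trial was sized, is supportive. The group main effect is not interpreted. Within-arm pre-post changes are descriptive only.

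In *Sample size, inclusion & exclusion criteria*, state the pre-post correlation used in the calculation. Add that the ANCOVA has at least the power of the sized interaction test (about 90% against 81% at correlation 0.5). This keeps the sizing and the main test consistent, so N need not change.

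Cost: wording only. The evoked-potential assessments are already made before and after training, so no new data are needed.
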